## Abstract

**Background:**

Cognitive behavioral therapy (CBT) is the most effective treatment for binge eating disorder (BED) but is limited by modest efficacy and low reach of in-person delivery. Combining mindfulness training with CBT could enhance efficacy by targeting emotion dysregulation, a key factor in BED that CBT does not adequately target. Digital delivery can enhance the reach of treatment. Accordingly, we developed *CBT-based Mindful Courage*, a 16-session digital intervention combining CBT and mindfulness training for BED.

**Objective:**

The aim of this study is to conduct a pilot randomized controlled trial to evaluate the feasibility (intervention and assessment completion) and acceptability (usability, overall satisfaction, engagement, visual appeal of content, understandability of program content, desire to continue the program, perceived skill acquisition, perceived confidence in implementing skills, and perceived helpfulness) of *CBT-based Mindful Courage*. We will also evaluate changes in outcomes (binge eating frequency, eating disorder symptoms, clinical impairment, and depression symptoms) and mechanisms (emotion dysregulation, dietary overrestriction, and trait mindfulness).

**Methods:**

This is a parallel-group, single-blinded, randomized controlled trial with a 1:1 allocation ratio. It will be conducted from November 2025 to November 2026, with study assessments at baseline, midtreatment, end-of-treatment, and 2-month follow-up. We will recruit a volunteer sample of adults with BED (N=40) aged 18 to 75 years via online advertisements. Exclusion criteria include a BMI <18.5, current anorexia or bulimia nervosa, and current treatment for BED or weight loss. Participants will be randomly allocated to an active control that includes coached self-monitoring (self-monitoring of food intake in *Recovery Record* and coaching calls by a research assistant) or to *CBT-based Mindful Courage+*coached self-monitoring. Both conditions will have a duration of 18 weeks. All study sessions will take place over Zoom.

**Results:**

The study was funded in April 2023. Data collection began in November 2025, and we anticipate recruitment to be completed by November 2026. Results are expected to be analyzed by May 2027 and published by May 2028.

**Conclusions:**

This will be an important first step in creating a scalable and efficacious treatment for BED.

**Trial Registration:**

ClinicalTrials.gov NCT07212673; https://clinicaltrials.gov/study/NCT07212673

**International Registered Report Identifier (IRRID):**

DERR1-10.2196/91761

## Introduction

Binge eating disorder (BED) is the most prevalent eating disorder (ED), affecting 17.3 million individuals worldwide [1]. Individuals with BED are at increased risk of several psychosocial and medical consequences [2-4] and elevated mortality [5]. Furthermore, BED is linked with high comorbidity [6] and reduced quality of life [7].

Conceptualizations of BED and other EDs have consistently focused on the notion that overrestriction (ie, excessive rigid restrictions in food intake) is a primary contributor to BED [8,9]. Consequently, cognitive behavioral therapy (CBT), the gold standard treatment for BED [10], has several behavioral components that directly target overrestriction [9].

However, CBT for BED has modest efficacy. Notably, approximately 50% of individuals who receive CBT for BED continue to report difficulties with binge eating after treatment [11]. The modest efficacy of CBT may be due to an inadequate focus on emotion dysregulation. Emotion dysregulation has been identified as a major contributing factor in the onset and maintenance of BED [12-14] but receives minimal attention in CBT treatments for BED. CBT interventions lead to only slight improvements in emotion dysregulation [8,15].

Mindfulness-based interventions (MBIs) are particularly effective for ameliorating emotion dysregulation [16,17] because they improve the ability to process and respond effectively to emotions. MBIs directly teach individuals to respond to emotions with awareness rather than automatically engaging in maladaptive emotion regulation strategies [18]. As such, they may help individuals with BED to accept emotions rather than react to them habitually (eg, by binge eating). Therefore, mindfulness training, the core component of MBIs, could be a promising addition to CBT for BED.

A few studies to date have investigated the use of MBIs in BED and produced preliminary evidence supporting the use of MBIs in the treatment of BED [19,20]. In addition, a recent review suggests that several MBIs for EDs result in significant reductions in emotion dysregulation [21]. Furthermore, our preliminary work indicates that MBIs result in large and significant decreases in emotion dysregulation in other EDs [22,23].

Integrating CBT and mindfulness training could lead to a potent intervention that targets two core mechanisms in BED: (1) excessive dietary restriction and (2) emotion dysregulation. Furthermore, mindfulness training may be synergistic with CBT. For example, mindfulness training may increase adherence to CBT skills by increasing the ability to tolerate emotional discomfort related to deploying CBT skills [24]. Similarly, CBT may enhance the ability to engage with the present moment and increase awareness by reducing focus on eating, weight, and shape.

Despite the promise of CBT and MBIs in the treatment of BED, a recent systematic review showed that only 20% of individuals in the community with a diagnosable ED can access ED-specific treatment [25] due to barriers such as a lack of experienced therapists, high cost of treatment, lack of health insurance, and shame and stigma associated with EDs and mental health treatment [26]. One way to overcome these barriers to treatment is to offer a digital treatment, that is, a multimedia application that can be delivered via smartphone or web. Digital MBIs and CBTs were already shown to be efficacious for several other psychiatric disorders [27-30]. While digital delivery of CBT has been shown to be efficacious for EDs [31], there are no digital MBIs to date for EDs outside of the ones developed in our preliminary work [22,23,32]. A recent meta-analysis of digital interventions for EDs included 8 treatments (4 for BED), and all interventions were based on CBT, with no interventions including mindfulness training [31]. Furthermore, the interventions included in this meta-analysis had various limitations, including high dropout rates, lack of engagement of the end user in the development stage, and modest effect sizes [31].

We developed a digital treatment combining CBT and mindfulness training for BED, called *CBT-based Mindful Courage.* We will conduct a small-scale randomized controlled trial (RCT) to assess the feasibility and acceptability of *CBT-based Mindful Courage*. The primary goals are to (1) evaluate feasibility, including intervention and assessment completion; and (2) evaluate acceptability, including dimensions of usability, overall satisfaction, engagement, visual appeal of content, understandability of program content, desire to continue the program, perceived skill acquisition, perceived confidence in implementing skills, and perceived helpfulness. Notably, the study is funded by the National Center for Complementary and Integrative Health (NCCIH) and guided by the NCCIH research framework [33] and the National Institutes of Health stage model for intervention development [34]. Accordingly, we will not conduct between-group analyses at this stage of development. Instead, we will evaluate within-treatment-condition mean changes in outcomes (binge eating frequency, ED symptoms, clinical impairment, and depression) and mechanisms (emotion dysregulation, dietary overrestriction, and trait mindfulness) as exploratory objectives.

## Methods

### Participant Recruitment and Eligibility Criteria

Participants will be recruited throughout the United States using advertisements posted on social media. The target sample size is 40 (n=20 in each treatment arm). This sample size was based on balancing various considerations, including ethical considerations (eg, participants’ time), resource use, prior feasibility trials [35], and availability of funding. Participant eligibility criteria are shown in Textbox 1.

Participant eligibility criteria.
**Inclusion criteria**
Aged 18 to 75 yearsAbility to speak English fluentlyMeeting *Diagnostic and Statistical Manual of Mental Disorders, 5th edition* criteria for current binge eating disorder (BED)Willing and able to commit to the entire study protocol
**Exclusion criteria**
BMI <18.5Requiring immediate treatment for medical complicationsHaving current anorexia or bulimia nervosa or purging behaviors within the past yearBeing pregnant or breastfeedingExperiencing other severe psychopathology or medical illness that would limit the participants’ ability to comply with the demands of this studyCurrently receiving BED or weight loss treatment (treatment for other conditions will be allowed, as long as the treatment is not mindfulness based)Currently taking medications for weight loss or beginning medications that affect eating or weight within the last 6 months

### Study Design

This study is a 2-arm pilot feasibility RCT with parallel assignment and a 1:1 allocation ratio. All procedures reported here are derived from protocol version 1.0. Participants will be randomized to one of the following groups: (1) coached self-monitoring or (2) *CBT-based Mindful Courage*+coached self-monitoring. Participants will be blinded as to whether they received the active intervention or control condition. Outcome assessors and data analysts will be blinded to group allocation. All recruitment and study activities will be conducted online; the principal investigator and study staff will be located at Yeshiva University. Participants will complete interview-based and self-report assessments assessed at baseline, midtreatment, end-of-treatment, and 2-month follow-up on Health Insurance Portability and Accountability Act (HIPAA)–secured Zoom.

### Ethical Considerations

#### Ethics and Participant Safety

This study has received approval from the institutional review board at Yeshiva University (43318060.0). To our knowledge, the intervention does not pose any significant risks to participants, although some participants may become distressed while engaging in the treatment because we are addressing sensitive content (eg, difficult emotions, ED urges, and eating). All questionnaires have been validated in numerous prior studies. However, some questionnaires involve questions on ED symptoms and diagnoses and other psychological difficulties, which may elicit distress in some participants. All participants will provide signed consent after being informed of study procedures and objectives, possible risks, and the right to withdraw from participation at any time.

#### Compensation

Participants will receive up to US $180 for completing study assessments. This will include US $20 for the baseline visit, US $30 for the midtreatment assessments, US $40 for the end-of-study assessments, US $60 for the 2-month follow-up assessments, and US $30 for completing all lessons (for participants in the *Mindful Courage*+coached self-monitoring condition only). We decided to provide incentivization for app adherence because we are in an early stage of treatment development, and we wanted to ensure that participants were fully exposed to the intervention to provide acceptability ratings.

#### Data Privacy and Security

All data will be collected and stored via Qualtrics. Qualtrics is HIPAA secured and uses industry-standard encryption, supports access controls, and has audit logs. Deidentified data will be stored on secure cloud servers and will be retained for a minimum of 5 years. Full access to data will be given only to the principal investigator and approved research staff. Zoom sessions will not be recorded.

### Overview of CBT-Based Mindful Courage

#### Core Lessons

The digital intervention *CBT-based Mindful Courage* was developed through an iterative process considering patient feedback and consists of 16 sequential core lessons, which are completed across 18 weeks (Multimedia Appendix 1). Each lesson takes approximately 40 to 50 minutes to complete and includes several key features to promote engagement [36-39], including multiple animated videos, audio-guided meditation practices, interactive activities and questions to help participants understand the intervention content in a personally relevant manner, and supportive feedback. After completing each core lesson, participants are instructed to complete 2 audio-guided mindfulness meditation sessions that last 10 to 15 minutes before the next core lesson. The program includes 2 narrators, both clinical psychologists, who appear as avatars in the animated videos to guide participants through the lessons. The program also features several fictional patients, voiced by professional actors hired through Fiverr, who share their experiences through client testimonials and discussions with the 2 psychologists.

The CBT content is derived from enhanced CBT for EDs [9] and a condensed CBT for EDs [40]. The mindfulness content is adapted from a digital MBI for substance use disorder (NCT05852015) developed by [name] et al [35], a prior digital MBI for anorexia nervosa developed by [name] et al [22,23], and several standardized MBI and acceptance and commitment therapy protocols [41-45], particularly mindfulness-based relapse prevention [41].

The intervention also combines CBT and mindfulness techniques. For example, (1) we combine self-monitoring and mindful awareness to increase awareness of eating patterns that may trigger binge eating, (2) we encourage mindful awareness of the consequences of irregular eating, (3) we instruct participants to use mindfulness strategies to notice in their daily life how using CBT strategies (such as reducing dietary restraint and eating satiating meals) affects hunger or fullness and binge eating urges, (4) we combine reduction of valuation of weight and shape with values work, (5) we encourage awareness of ED behaviors and of the relationships between ED behaviors and ED symptoms, and (6) we encourage awareness of factors that may contribute to lapses and relapses.

#### Animated Content

The animated videos were built with Powtoon, an online animation creation program; the digital lessons were created in Qualtrics; and videos were hosted in Vimeo. Audio content was recorded and edited with Audacity. See Figure 1 for examples of *CBT-based Mindful Courage* visuals.

**Figure 1 figure1:**
[figure not shown]
Example animations and video clips of cognitive behavioral therapy (CBT)–based Mindful Courage. BOAT: Breathe, Observe, Accept, Take a Moment; ED: eating disorder; SOAK: Stop, Observe, Appreciate, Keep Curious.

### Overview of Coached Self-Monitoring

#### Recovery Record

Participants in both conditions will be asked to self-monitor their food intake using *Recovery Record* [46], a frequently used digital intervention among individuals with BED [47]. Participants will not be asked to engage with any other features of *Recovery Record.* We chose to ask participants from both conditions to track their food intake as regular eating is the foundation of ED recovery [48].

#### Phone Coaching

Participants in both conditions will receive phone coaching by psychology students during the 18-week treatment period but not during the follow-up period. Phone coaching for both conditions will include weekly coaching calls (10-15 minutes, except for week 1, which will be 30 minutes) and extra technical support as needed via phone and SMS text message. In addition, for participants in *CBT-based Mindful Courage*, there will be 1 to 2 weekly SMS text message reminders to use *CBT-based Mindful Courage* and additional phone or SMS text message contact (up to 1 weekly call and 2 weekly SMS text messages) for participants not engaging in *CBT-based Mindful Courage*. The aim of the phone coaching is to provide general motivational and technical support rather than provide any specific therapeutic intervention.

### Treatment Conditions

#### Coached Self-Monitoring

Participants in this condition will not have access to *CBT-based Mindful Courage* but will be asked to self-monitor their food intake in *Recovery Record* and will receive phone coaching.

#### CBT-Based Mindful Courage+Coached Self-Monitoring

Participants in this condition will have access to *CBT-based Mindful Courage* for 18 weeks. Participants will also be encouraged to engage with *Recovery Record* self-monitoring of food intake and will also receive phone coaching.

### Measures

Multimedia Appendix 2 [49-61] provides a summary of assessments and measures.

#### Screening Measures

We will establish BED diagnosis using the Structured Clinical Interview for *Diagnostic and Statistical Manual of Mental Disorders, 5th edition* [49]. Other inclusion criteria will be assessed with 1-item questions in an interview-based assessment.

#### Feasibility Benchmarks

Benchmarks for feasibility are based on previous digital interventions for EDs [31,62-64], and include (1) feasibility of recruitment (40 participants randomized); (2) feasibility of randomization (75% of eligible screens randomized); (3) intervention completion (34/40, 85% of randomized individuals completing at least 1 module; average completion rates of 60% for the 16 lessons) assessed objectively via Qualtrics; (4) completion rates for midtreatment, end-of-treatment, and 2-month follow-up visits (32/40, 80% of participants completing the midtreatment visit, 30/40, 75% of participants completing the end-of-treatment visit, and 26/40, 65% of participants completing the follow-up visit).

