### Statistical Analysis

#### Feasibility and Acceptability

We will use descriptive statistics to examine feasibility and acceptability of *CBT-based Mindful Courage*. Both groups will be included in analyses of recruitment feasibility, randomization, and assessment completion, whereas only participants in the *CBT-based Mindful Courage* group will be included for evaluating acceptability and feasibility of intervention completion. Specifically, we will compute average scores and frequencies for all feasibility and acceptability benchmarks.

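### The intervention-completion benchmark is printed as 34 of all 40 randomized, but only the 20 in the intervention arm have modules to complete; 85% of that arm is 17/20

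*Protocol article*

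**What the plan says.** The relevant statements are all in the protocol article.

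- **Feasibility Benchmarks**, item 3, sets intervention completion in two parts. The first is "34/40, 85% of randomized individuals completing at least 1 module". The second is "average completion rates of 60% for the 16 lessons". Completion is to be measured objectively through Qualtrics. Item 4 of the same list gives visit-completion benchmarks of 32/40, 30/40 and 26/40.
- **Study Design**: "This study is a 2-arm pilot feasibility RCT with parallel assignment and a 1:1 allocation ratio". The section on recruitment and eligibility plans 40 participants, 20 per arm.
- **Treatment Conditions**, on the control arm: "Participants in this condition will not have access to" the program. On the other arm: "Participants in this condition will have access to *CBT-based Mindful Courage* for 18 weeks". The section on randomization and the baseline session likewise gives access instructions and session 1 only to the intervention arm.
- **Statistical Analysis, Feasibility and Acceptability**: both groups count for recruitment, randomization and assessment completion, but only the program "group will be included for evaluating acceptability and feasibility of intervention completion".

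**The concern.** The benchmark counts people who complete at least one module, as a share of everyone randomized. Half of those people are never offered a module. The numerator is therefore capped by the size of one arm while the denominator covers both, and the required count of 34 exceeds the number who could contribute to it.

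The Introduction makes feasibility, including intervention completion, a primary goal, and the Discussion expects the results to set the stage for an efficacy trial. This is one of a small number of numeric criteria against which that goal will be judged. If it stays as printed, the report must either declare a failure that no uptake could have avoided, or state a threshold different from the published one and explain why. A correction dated before analysis avoids both.

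**Working it through.** **Inputs**

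- Total randomized, planned: 40. Per arm: 20 (recruitment and eligibility section; 1:1 allocation in Study Design).
- Benchmark: 34/40, 85% (Feasibility Benchmarks, item 3).
- Participants with access to modules: intervention arm only, 20 (Treatment Conditions; randomization and baseline session).
- Analysis group for intervention completion: intervention arm only (Statistical Analysis).

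**Step 1. Reproduce the printed figure.** 0.85 × 40 = 34, and 34/40 = 85.0%. The count and percentage agree with each other, but only when all 40 randomized form the denominator.

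**Step 2. Highest attainable result on that denominator.** If every intervention participant completes a module, the count is 20, so the share is 20/40 = 50.0%. The shortfall is 34 − 20 = 14 participants, or 85 − 50 = 35 percentage points.

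**Step 3. The printed count on the analysis group.** 34/20 = 170%, which is impossible. The count of 34 cannot be carried over to the group that the Statistical Analysis section names.

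**Step 4. The printed percentage on the analysis group.** 0.85 × 20 = 17, so the threshold is 17/20, which is attainable. On the printed denominator, the same 17 completers would appear as 17/40 = 42.5%.

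**Step 5. The neighbouring benchmarks.** 32/40 = 80%, 30/40 = 75% and 26/40 = 65%. These three are consistent: both arms attend the assessments, and the Statistical Analysis section includes both groups for assessment completion. A denominator of 40 is right for them and wrong for module completion.

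**Step 6. Could a control participant complete a module?** Both arms use Recovery Record and receive phone coaching, but neither is described as a module. The benchmark is measured in Qualtrics, where the section on animated content says the digital lessons were created, and the same item goes on to refer to the 16 lessons. I found no reading of the word that brings the control arm into the numerator.

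**The case against.** The strongest reply is that the article already settles the matter. The Statistical Analysis section assigns each feasibility measure to its group and places intervention completion in the program arm. An analyst following it would use the 20 intervention participants, apply 85%, and reach a sensible answer. The benchmark is also descriptive, no stop or progression rule is tied to it, and the second part of the same item, the 60% average over lessons, has no printed count and is unaffected.

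Much of this stands, and it rules out two stronger readings that a reader might infer. One is that the denominator would have to be picked once the results are known. The documents do not support that, because the analysis group is specified in advance. The other is that the trial is bound to fail its completion criterion. That follows only if the Statistical Analysis section is ignored; the 85% can be met on the group it names.

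The reply does not remove the error. The benchmark gives an explicit count, denominator and population, and all three conflict with the section that is said to govern them. This is not detail left to a fuller document, since the article states the figure and states it wrongly. Nor does it look like a text-extraction fault, since 34, 40 and 85% agree with one another.

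A further fair caution is that 17/20 is printed nowhere. It is inferred from the stated percentage and the stated analysis group, and the sources cited for the benchmarks are not at hand to confirm it.

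One neighbouring matter is separate from this point: intervention participants complete session 1 within the baseline visit, so even a corrected benchmark would largely reflect attendance at that visit.

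**Conclusion.** The point holds as a contradiction between the printed benchmark and the trial's own design and analysis section. As printed, the benchmark cannot be met: at most 20/40 (50%) against 34/40 (85%). Applied to the intervention arm, 85% is attainable and corresponds to 17/20. The error lies in the count and in the population named, not in the percentage as such.

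The conclusion assumes the planned arm size of 20. Urn randomization may leave the arms slightly unequal, but that would not rescue the printed figure: at least 34 of the 40 would have to be allocated to the intervention, which is incompatible with 1:1 allocation. It also assumes that a module is a lesson of the digital program, which the measurement in Qualtrics supports. That 17/20 is what the authors meant is a strong inference, not something the article states.

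**What to change.** Before analysis, and with a date, restate the first part of the intervention-completion benchmark under Feasibility Benchmarks as: 85% (17/20) of participants randomized to CBT-based Mindful Courage+coached self-monitoring complete at least one module. This matches the Statistical Analysis section, which needs no change. The sponsor should confirm that 85% of that arm is the intended threshold. The visit-completion benchmarks keep their denominator of 40.

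The cost is one line of text. Sample size, randomization, data collection and participant procedures are unaffected.

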#### Randomization and Baseline Session

If participants are eligible and willing to continue, they will be randomly assigned to either coached self-monitoring or *CBT-based Mindful Courage*+coached self-monitoring by the psychology student who completed the screening interview. Following our prior work [35], randomization will be achieved using a web-based computerized urn randomization program that ensures balance across treatment groups based on sex, age, binge eating severity, and race or ethnicity. Allocation concealment will be ensured because the program reveals assignments only after participant enrollment. After randomization, participants will proceed to the baseline study session (also conducted over Zoom by the psychology student; Multimedia Appendix 2) and will be instructed on how to track their food intake in *Recovery Record.* They will also receive the orientation for phone coaching. Participants randomized to the *CBT-based Mindful Courage*+coached self-monitoring condition will be instructed on how to access *CBT-based Mindful Courage* (either on their computers or via Android or iPhone) and will complete session 1 of the intervention as part of the visit. After completing session 1, participants will be informed that they will have 18 weeks of access to the app to complete 16 lessons and the 2 accompanying mindfulness practices, with weekly support from a student coach.

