## Discussion

### Anticipated Findings

This protocol describes the design of a pilot RCT with the primary objectives of evaluating the feasibility and acceptability of a digital program combining CBT and mindfulness training for BED—*CBT-based Mindful Courage*. As exploratory objectives, we will evaluate changes in binge eating frequency, global ED symptoms, clinical impairment, and depressive symptoms (as outcomes), as well as emotion dysregulation, dietary overrestriction, and trait mindfulness (as potential mechanisms).

On the basis of our prior research [22,23,32], we anticipate that *CBT-based Mindful Courage* will be acceptable and feasible, setting the stage for an efficacy trial. Our recent study evaluating an 8-week version of *Mindful Courage* for anorexia nervosa and bulimia nervosa concluded that intervention feasibility was excellent and that the intervention was acceptable to participants [23]. Furthermore, our pilot trial evaluating a single-session version of *Mindful Courage* for BED demonstrated excellent acceptability and 100% intervention completion [32]. Preliminary efficacy was demonstrated in both cases, with significant improvements in ED symptoms as well as secondary outcomes (eg, clinical impairment).

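### On the intervention arm, the completion benchmark of at least one module is met almost automatically, because session 1 is done inside the baseline visit

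*Protocol article*

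**What the plan says.** Feasibility Benchmarks gives intervention completion two criteria, the first printed as 34/40 and both assessed through Qualtrics: "85% of randomized individuals completing at least 1 module; average completion rates of 60% for the 16 lessons".

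Randomization and Baseline Session fixes the order of events: "After randomization, participants will proceed to the baseline study session (also conducted over Zoom by the psychology student". In that session, participants allocated to CBT-based Mindful Courage "will complete session 1 of the intervention as part of the visit". Only afterwards are they told that they have 18 weeks to work through the 16 lessons.

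Three other statements settle who is counted:
- Sample size (Participant Recruitment and Eligibility Criteria): "The target sample size is 40 (n=20 in each treatment arm".
- Analysis set (Statistical Analysis, Feasibility and Acceptability): only the CBT-based Mindful Courage "group will be included for evaluating acceptability and feasibility of intervention completion".
- Control arm (Coached Self-Monitoring): "Participants in this condition will not have access to" the programme.

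**The concern.** Intervention completion is part of the first primary goal, and the Strengths and Limitations section names dropout from treatment as the first expected problem. Of the two completion criteria, the one on at least one module is the only one that counts participants. An average over lessons cannot tell broad uptake from heavy use by some participants and none by the rest; a count of participants can.

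That count can be satisfied before anyone has to return to the programme. A participant who finishes the baseline visit and never opens another lesson scores the same as one who finishes all 16. What is at stake is whether a feasibility conclusion could be reported while a sizeable minority of the arm made no use of the intervention after the visit.

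**Working it through.** **Inputs.** From the protocol article: 40 randomized, 20 per arm; 16 lessons; thresholds of 85% (at least one module) and 60% (average of the lessons); session 1 completed within the baseline visit; intervention completion assessed in the intervention arm only. Module 1 is taken to be session 1. The article uses module, lesson and session without defining them, but this is the natural reading.

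**1. The printed figure.** 0.85 × 40 = 34, so 34/40 reproduces. Controls have no access, so at most 20/40 = 50% can ever be reached on that denominator. On the stated analysis set the threshold is 0.85 × 20 = 17, that is, 17/20. The rest uses 17/20.

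**2. First criterion with no later use.** If all 20 finish session 1 in the visit and nobody continues, the result is 20/20 = 100%: met. It fails only at 16/20 or fewer, so at least 4 of 20 must be lost between randomization and the end of session 1.

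Chance of passing, P(X ≥ 17) for X binomial with n = 20, if a proportion p finishes session 1 in the visit. The article gives no p, so these are assumed values:

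| p | Chance of passing |
|---|---|
| 0.98 | 0.9994 |
| 0.95 | 0.984 |
| 0.90 | 0.867 |

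Later use does not enter this calculation.

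**3. What the 60% average catches.** Total lessons are 16 × 20 = 320, and 60% is 192. Let k participants stop after session 1 and the other 20 − k complete everything. The highest possible average is (k + 16(20 − k))/320. For 60% to be met, the others must average at least (192 − k)/(20 − k) lessons.

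| k stopping after session 1 | Highest possible average | Lessons the others must average |
|---|---|---|
| 4 | 260/320 = 81.3% | 188/16 = 11.75 |
| 6 | 230/320 = 71.9% | 186/14 = 13.3 |
| 8 | 200/320 = 62.5% | 184/12 = 15.3 |
| 9 | 185/320 = 57.8% | not attainable |
| 10 | 170/320 = 53.1% | not attainable |
| 20 | 20/320 = 6.25% | none left |

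Both benchmarks can therefore be met with up to 8 of 20 (40%) making no use after the visit.

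**4. The same 85% applied to use after the visit.** Requiring 17/20 to complete at least one lesson after the visit fails for every k of 4 or more. For k from 4 to 8 this can turn a pass on both benchmarks into a fail on one.

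**The case against.** The case on the other side is substantial, and much of it stands.

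- **The criterion can fail.** A reader might infer that it is met by construction. Session 1 comes after randomization and takes about 40 to 50 minutes, so losses in that interval count against it; four are enough. This stands. Met almost automatically is as far as the text goes.
- **As printed, it cannot pass.** On 34/40 the criterion is out of reach. The concern applies once the denominator is corrected, and correcting only the denominator would leave the weakness in place.
- **The companion benchmark protects against gross failure.** A reader might infer that feasibility could be declared with half the arm never returning. With both benchmarks applied that is false: the average is then at most 53.1%. The article does not say whether both must be met, but it commits to reporting all benchmarks and nowhere lets the easier one decide alone. What the average does not catch is a group of 4 to 8 who stop at once while the others do well.
- **Session 1 is a real lesson.** One might also object to its counting toward the 60%. The visit supplies 20 of the 192 lessons needed, leaving 172 of the other 300 (57.3% rather than 60%). That is 2.7 points, and counting one of the 16 core lessons is legitimate. Excluding it would be a preference.
- **Supervision is not stated.** The visit is run by a psychology student, but the article does not say that the lesson itself is led. The point rests only on when the lesson is done.
- **The single-session pilot proves little here.** Anticipated Findings reports that this version "demonstrated excellent acceptability and 100% intervention completion". It was a different version in another study and does not establish completion of this trial's baseline visit.
- **The benchmark may come from earlier studies.** The article says the benchmarks follow previous digital interventions. Those sources are not available here, so comparability may have been the reason for the wording.

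**Conclusion.** The point holds in a limited form. On the intervention arm, the criterion of at least one module measures completion of the baseline visit and says almost nothing about uptake of the programme afterwards. The completion assessment as a whole is not blind, because the 60% average would reveal widespread non-use. The gap lies between 4 and 8 of 20 participants (20% to 40%) stopping after session 1: the participant-level criterion does not register them, and the average can still pass if the others complete enough.

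The upper end is demanding, since at 8 the other 12 must average at least 15.3 of 16 lessons. At 4 they need only 11.75.

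This rests on module 1 being session 1, on that session counting toward the benchmark (nothing excludes it), and on all 20 finishing it in the visit.

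**What to change.** In Feasibility Benchmarks, restate the first completion criterion as 85% of participants randomized to CBT-based Mindful Courage (17/20) completing at least one lesson after the baseline visit. Report session 1 completion separately as treatment initiation. Leave the 60% average over 16 lessons as it is. The same edit removes the unreachable 34/40.

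The Results section says data collection began in November 2025, so the change should be made and dated before completion data are examined.

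The cost is small: one reworded sentence and no new data, since completion is already assessed through Qualtrics. There are two drawbacks. The reported figure will be less favourable and less directly comparable with any earlier study that used at least one module. The criterion also becomes demanding at n = 20: at assumed true uptake after the visit of 70%, 85%, 90% and 95%, the chance of reaching 17/20 is 10.7%, 64.8%, 86.7% and 98.4%. The team should confirm that 85% is the level it wants for use after the visit.
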